### Study design

We will conduct a mixed methods feasibility study using an exploratory framework. The quantitative component will be a stepped-wedge cluster randomized controlled trial. All study sites will have uniform access to their usual Waterloo Wellington Local Health Integration Network geriatric services. Using a computer-generated sequence and simple randomization techniques, we will randomize the order of when each site acquires access to GeriMedRisk. Every 8 weeks, a new site will gain access to the intervention until all four LTC sites have access to the intervention (Fig. 1). This time period allows for the orientation and potential adoption of GeriMedRisk and telemedicine technology prior to introducing the next site.

**Fig. 1 Fig1:**
[figure not shown]
Schematic of study protocol. Each step from T0 to T3 will be approximately 8 weeks in length. Each cell starting at T0 represents a data collection point. Prior to T0, secondary outcomes will be collected retrospectively collected using the RAI-MDS 2.0. Yellow-shaded cells represent the recruitment period. During this time, LTCs will be invited to participate and will be provided trial information. Consent will be obtained from each LTC. Subsequently, investigator will provide in-person and online information sessions about the trial to potential participants (i.e., clinicians of the participating LTC site), and consent will also be obtained. Randomization (red line) will occur at the beginning of the first step, T0. The GeriMedRisk intervention (dark blue cells) will then be introduced to each LTC in random order. At the beginning of each step, a sealed envelope will be opened to reveal the next LTC to receive the intervention. An interim analysis (green line) will be performed at 16 weeks

### Recruitment

At the commencement of GeriMedRisk access, there will be an initial informative site visit scheduled at a time to reach all the site’s LTC clinicians to introduce them to the study and GeriMedRisk including the various methods of accessing the intervention. Investigators will approach the participants (referring clinicians) in meetings facilitated by the long-term care facility at a time that is convenient for the participants. Flyers describing the intervention will be available for posting at the long-term care facility clinical staff areas once the LTC site (cluster) has access to the intervention. Although residents are not subjects of the study, we will notify them or their substitute decision-makers about the study upon the site’s introduction to the intervention until its conclusion and provide the option and instructions (LTC site-specific individual and their contact information) to opt out of the service.

### Outcomes

#### Primary outcome

Primary outcome measures of this trial are the feasibility and acceptability of the GeriMedRisk intervention, outcome measures, and study design. These include the monthly number and proportion of clinicians who use or decline GeriMedRisk per long-term care home, the number of patients or their substitute decision-makers who decline a GeriMedRisk consultation, and the number of consults, wait times for telephone (ring, queue and call time, or the number of dropped calls), or the OTN eConsult (defined as the times from the initial consult request to first contact and to when the consultation is provided). We will assess the time required for each consultation and follow-up encounter with the referring clinician. We will quantitatively measure satisfaction by measuring the proportion of GeriMedRisk recommendations that were executed by the referring clinician or the number of repeat referring clinicians. We define a priori threshold for acceptability as:The proportion of GeriMedRisk recommendations that were executed would be 60% or more [25, 26].The proportion of repeat referring clinicians per LTC site would be > 20% or more.

To identify human resources needs, we will measure the monthly number of consultations requiring physician support with geriatric medicine, clinical pharmacology, and geriatric psychiatry expertise. We will characterize the number of complex cases defined as a case either involving polypharmacy (four or more medications) [27] or requiring physician support or three or more follow-up encounters. We will also assess the financial feasibility of GeriMedRisk through salary and physician billings data [13].

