### Intervention

In addition to the usual Waterloo-Wellington regional geriatric services, clinicians caring for seniors with medication challenges will have access to GeriMedRisk. GeriMedRisk is an interdisciplinary, technology-based geriatric pharmacology consultation and review service. It aims to optimize a patient’s medications to improve cognition, mobility, function, and mental health by supporting their clinicians. Referring clinicians will be able to easily access GeriMedRisk nurses, pharmacists, and physicians specializing in geriatric medicine, clinical pharmacology, and geriatric psychiatry by telephone or through telemedicine during business hours. Input from the following informed GeriMedRisk’s development: long-term care residents and their caregivers; Waterloo-Wellington region health administrators; the Ontario Poison Centre, a provincial service that uses telemedicine to deliver toxicological expertise to the public and clinicians in Ontario, Canada; the Ontario Telemedicine Network; and Champlain BASE eConsult and a needs assessment of Waterloo-Wellington physicians, nurse practitioners, pharmacists about geriatric pharmacotherapy.

Participants have two options for methods for referral:Telephone: this traditional mode of person-to-person consultation can be either real-time or delayed by a few hours if used as a paging service whereby the referring clinician leaves a call-back number.eConsult: the referring clinician sends an eConsult with the patient’s necessary clinical information through a private and secure portal through the Ontario Telemedicine Network (OTN) at www.otnhub.ca to GeriMedRisk [12]. The GeriMedRisk team responds within five business days through eConsult with a request for additional information or recommendations. Additional support through the phone, OTN videoconference or in-person may be arranged if necessary.

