### Data collection

#### Primary and secondary outcomes

The primary outcomes of this study include the acceptability and feasibility of GeriMedRisk and the stepped-wedge cluster randomized controlled trial. These include factors influencing the successful implementation of the GeriMedRisk service in terms of feasibility and acceptability among users and non-users and staff providing the GeriMedRisk service. Secondary outcomes include the LTC site’s monthly rate of falls, hospital visits, and medication appropriateness. We will measure secondary outcomes in the 52-week period preceding the commencement of GeriMedRisk access (defined as day − 365 to the first day of access to GeriMedRisk) and after, on a monthly basis for each site. These pre-specified outcomes will be systematically collected from our project-specific database from the OTN eConsult database, telephone records, RAI-MDS 2.0, and physician billings.

The Ontario Telemedicine Network (OTN) database is an administrative database that contains physician contact information and specialty and dates of engagement with GeriMedRisk. We will utilize telephone records as measured by the Voice Over Internet Protocol telecommunications manager, Vertical Summit®, to capture call volumes, dropped calls, and ring, queue, and call times. We will use the RAI-MDS 2.0 data for each LTC site. This standardized assessment tool is routinely applied to all LTC residents in Ontario, Canada, upon LTC admission, readmission from the hospital, change in status, and on a quarterly basis [30–32, 34]. It captures demographical and clinical information that is frequently used in observational research and quality improvement initiatives. We will use de-identified and anonymized aggregate data from the RAI MDS for each LTC site. We will also use aggregated, anonymized, and de-identified LTC pharmacy records to obtain information about prescription and non-prescription medication use.

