## Discussion

If GeriMedRisk is a feasible intervention, it would be the first technology-based interdisciplinary geriatric pharmacology intervention in Canada. The risks of participating in this GeriMedRisk study include the clinician participant’s time involved for each consult and follow-up. Although each consult may take up to 45 min on the telephone, this time could be significantly decreased by contacting GeriMedRisk through the secure OTN eConsult platform. The benefits of participating in this study include access to geriatric pharmacology expertise in a timely fashion without patient travel to an urban academic health center. Participants will also have the opportunity to provide feedback about GeriMedRisk to help improve the service and its impact on real-world practice. Finally, participants will have access to a service that supports their continuing professional development through concise learning materials pertinent to their patients and quarterly summaries of their learning issues generated from their consults. There will be no cost to participants for these services. By understanding the experiences and perceptions of GeriMedRisk stakeholders, we will be able to provide generalizable information about feasibility and acceptability for the wider health community, refine both referral criteria and mode of delivery for the subsequent clinical trial, inform the potential rollout of the intervention to other healthcare sectors, and further develop the consultation service.

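### Telephone wait time, as defined, has no component for the call-back delay of paged referrals and lists call time as if it were waiting

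*Protocol article*

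**What the plan says.** Under Outcomes, Primary outcome, the article lists "wait times for telephone (ring, queue and call time, or the number of dropped calls" as a feasibility measure. The same sentence gives eConsult its own clock, "defined as the times from the initial consult request to first contact and to when the consultation is provided". As punctuated, that clock belongs to eConsult only.

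The next sentence adds a separate measure: "We will assess the time required for each consultation and follow-up encounter with the referring clinician".

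Under Intervention, telephone referral "can be either real-time or delayed by a few hours if used as a paging service whereby the referring clinician leaves a call-back number".

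Under Data collection, Primary and secondary outcomes, the telephone system is to be used "to capture call volumes, dropped calls, and ring, queue, and call times". These are the same items as in the outcome definition, with call volumes added. A project-specific database is also named as a source, but its fields are not listed.

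**The concern.** When a clinician leaves a number and waits for a return call, the wait is the interval between the two calls. The plan expects this to happen and expects it to last hours, yet the components it names stop when the first call ends and start again when the return call rings. A paged referral that took an afternoon to answer could appear in the results with only a few minutes of ring and queue time.

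Call time raises a second problem. Once the clinician is speaking to the service, waiting has ended. The Discussion says that "each consult may take up to 45 min on the telephone", so this is not a trivial component, and it already has a home in the consultation-duration measure.

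What is at stake is whether the feasibility results can show how quickly the telephone service responds. Timely access is one of the benefits that the Discussion claims. If call-backs are slow, the measure as written cannot reveal it, and call-back times that are not logged prospectively may be hard to recover.

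**Working it through.** No sample size, power or threshold in the article depends on wait time, so there is no stated figure to reproduce. The check sets the definition against the described service and then bounds the gap.

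**Step 1. What each component covers**

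| Interval in a telephone referral | Live call | Paged call | Covered by the definition? |
|---|---|---|---|
| Ring and queue | yes | yes | yes |
| Leaving a call-back number | no | yes | yes, as call time |
| Number left until return call | none | a few hours | **no** |
| Conversation with the service | yes | yes | yes, as call time, though this is not waiting |

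The number of dropped calls is a count and fills no interval. The consultation-duration measure is a length of contact and does not fill the gap either.

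**Step 2. Inputs for the size**

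- Delay *d*: the article says only a few hours. Assumed 2, 3 and 4 h.
- Share of telephone consults that are paged, *s*: not given. Assumed 10%, 25% and 50%.
- Call length *c*: up to 45 min (Discussion). Assumed 15 to 45 min.

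**Step 3. Mean wait missed**

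Missed minutes per telephone consult, averaged over all calls = *s* × *d* × 60.

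| Paged share | 2 h | 3 h | 4 h |
|---|---|---|---|
| 10% | 12 | 18 | 24 |
| 25% | 30 | 45 | 60 |
| 50% | 60 | 90 | 120 |

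The smallest value is 0.10 × 2 × 60 = 12 min and the largest is 0.50 × 4 × 60 = 120 min. For a single paged call the whole 2 to 4 h is missed; for a live call nothing is missed.

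**Step 4. If call time were added into the wait**

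The article does not say that the components are summed. If they were, call time would push the other way:

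- For one paged call, the omission still dominates. With the shortest assumed delay and the longest call, 120 − 45 = 75 min remain unrecorded.
- For the mean over all calls, adding *c* minutes per consult offsets the omission until *s* exceeds *c* / (60 × *d*). That break-even share runs from 15/240 = 6.25% (15 min call, 4 h delay) to 45/120 = 37.5% (45 min call, 2 h delay).

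So for paged referrals the direction is the same on either reading. For the overall mean, the direction is certain only when ring and queue time are taken alone.

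**The case against.** The strongest reply is that these are telephone-system indicators, to be reported one by one. The list includes a count, which cannot be added to minutes, and the data-collection section names the items as separate captures. Read that way, call time would be visible as call time. This stands, and it removes any claim that a long live call would be made to look slower than a slow call-back: that result needs a sum the article never specifies. It does not help with the call-back interval, which is missing however the items are reported.

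A second reply is that a condensed article need not list every time stamp, and the project-specific database may hold them. That is possible. But the definition of telephone wait is stated, its components are listed and its source is named. A call-back field elsewhere would not enter the measure as written.

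Two stronger inferences are tempting, and the documents do not support them:

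- **A reader might infer that a telephone-versus-eConsult comparison is biased in favour of telephone.** No such comparison is planned; the primary outcomes are described narratively with confidence intervals where appropriate. Nor is it shown that the order would change on a common clock. For eConsult, "The GeriMedRisk team responds within five business days through eConsult with a request for additional information or recommendations", against a few hours for a paged call, so telephone could well remain faster.
- **A reader might infer that the way the service is delivered in the next trial will be settled on these wait times.** The Discussion ties that refinement to what stakeholders experience and perceive, and no passage ties it to wait times.

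**Conclusion.** The point holds in a limited form. The stated telephone definition omits a delay that the same article describes, so the wait is understated for every paged referral, and call time is misplaced under waiting. Live calls are not understated.

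The illustrative range of 12 to 120 min of mean wait rests entirely on the assumed paged share and delay. If nearly all calls are live, the gap is small.

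The consequence is confined to how feasibility is described. Wait time has no threshold and plays no part in the acceptability rule, which rests on 60% adherence to recommendations or 20% repeat use. The sample size does not depend on it.

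**What to change.** In Outcomes, Primary outcome:

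1. Define telephone wait as the time from the first call, or from the message left, to first contact with GeriMedRisk staff, and to when the consultation is given. This is the eConsult clock. State that for a paged referral, first contact means the return call and not the taking of the number.
2. Record the call-back request and return times, either as logged time stamps or by matching each return call to its originating call.
3. Report live and paged calls separately, with the number of each.
4. Keep ring time, queue time and dropped calls as measures of the telephone system.
5. Report call time under the consultation-duration measure.

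The cost is a change of wording plus the work of logging time stamps or matching call records. The reported telephone wait will probably look less favourable. Neither the design nor the sample size changes.

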#### Secondary outcomes

The core outcome set for effectiveness trials aimed at optimizing prescribing in older adults in care homes informed the selection of our secondary outcomes [28, 29]. These outcomes are clinically relevant, potentially modifiable, well-validated in the MDS-RAI 2.0, and in some cases, a surrogate marker of care [30–32]. For these same reasons, Health Quality Ontario, a provincial body that advises on the quality of health care provided, also uses these outcomes as long-term care quality indicators [32]. We will assess the completion of our secondary outcome data regarding each LTC site’s monthly rates of falls, hospital visits, and medication appropriateness. Using the Resident Assessment Index Minimum Data Set (RAI-MDS) 2.0, we will examine the following in the 1-year lookback period prior to the date of the intervention’s introduction and monthly thereafter [30]. We will examine each LTC site’s monthly incidence of falls and injurious falls and emergency hospital visits. We will include all-cause mortality and those associated with adverse drug events or falls [28]. We will characterize the proportion of LTC residents receiving potentially inappropriate medications defined by the Beers Criteria and STOPP/START criteria [4, 33], psychotropics (defined as a sedative-hypnotic, antidepressant, antianxiolytic, antipsychotic, lithium or antiseizure medication in the absence of a seizure diagnosis), and long-acting opioids.

### Randomization and allocation

Access to GeriMedRisk (intervention) will be sequentially and randomly rolled out over 8-week periods. The sequence will be randomly generated by a computer model and simple randomization techniques. The allocation sequence will be concealed in sequentially numbered, opaque, sealed envelopes that will be opened at the beginning of each step.

#### Blinding

The LTC sites (clusters) will be blinded to the allocation sequence. None of the LTC sites’ clinicians or administrators work across the sites. There will also be blinding of the data analysis. The secondary outcomes are systematically collected by nurses, nursing managers, and the LTC administration, in the RAI-MDS 2.0, as part of their mandated reporting to the Ministry of Health and Long-Term Care. By retrospectively collecting the secondary outcomes in the 12 months preceding the intervention (lookback period), this ensures blinded data collection of the LTC patient demographic and clinical variables for this period. During the study, the secondary outcome data will continue to be collected by the same LTC team. Since nurses and nursing managers involved in multidisciplinary patient care are key to geriatric patient care, it would not be ethical to blind them, or any clinicians, involved in the patient’s care. The LTC pharmacy records are administrative databases that automatically capture prescription and non-prescription medication use among LTC residents. Only aggregated, anonymized, and de-identified pharmacy records of the LTC will be used for the secondary outcomes. There will be no blinding procedure for patients and their caregivers. We will not remove blinding from individuals involved with data collection or analysis processes. For the qualitative evaluation, there will be no blinding procedure.

### Data collection

#### Primary and secondary outcomes

The primary outcomes of this study include the acceptability and feasibility of GeriMedRisk and the stepped-wedge cluster randomized controlled trial. These include factors influencing the successful implementation of the GeriMedRisk service in terms of feasibility and acceptability among users and non-users and staff providing the GeriMedRisk service. Secondary outcomes include the LTC site’s monthly rate of falls, hospital visits, and medication appropriateness. We will measure secondary outcomes in the 52-week period preceding the commencement of GeriMedRisk access (defined as day − 365 to the first day of access to GeriMedRisk) and after, on a monthly basis for each site. These pre-specified outcomes will be systematically collected from our project-specific database from the OTN eConsult database, telephone records, RAI-MDS 2.0, and physician billings.

The Ontario Telemedicine Network (OTN) database is an administrative database that contains physician contact information and specialty and dates of engagement with GeriMedRisk. We will utilize telephone records as measured by the Voice Over Internet Protocol telecommunications manager, Vertical Summit®, to capture call volumes, dropped calls, and ring, queue, and call times. We will use the RAI-MDS 2.0 data for each LTC site. This standardized assessment tool is routinely applied to all LTC residents in Ontario, Canada, upon LTC admission, readmission from the hospital, change in status, and on a quarterly basis [30–32, 34]. It captures demographical and clinical information that is frequently used in observational research and quality improvement initiatives. We will use de-identified and anonymized aggregate data from the RAI MDS for each LTC site. We will also use aggregated, anonymized, and de-identified LTC pharmacy records to obtain information about prescription and non-prescription medication use.

#### Qualitative outcomes

Qualitative data collection will be collected through semi-structured interviews, surveys, and staff consult reflection notes. A team of researchers, not involved in patient care, generated questionnaires based on the theoretical domains framework (TDF) for GeriMedRisk staff, LTC clinicians to understand the barriers, and facilitators to implementation and acceptability of GeriMedRisk [35]. The TDF-based questionnaire will be administered to GeriMedRisk staff throughout the intervention implementation. This survey will be sent to all LTC clinicians. We will choose a census sampling approach as the expected numbers of potential GeriMedRisk service users per LTC site will not be large. We will send the questionnaire to a convenience sample of non-referring clinicians, defined as clinicians who practice at the LTC but did not consult during the study period. A total of three email or telephone reminders for the survey will be sent out every 2 weeks to optimize the response rate. Additionally, GeriMedRisk staff will engage in and document self-reflection activities to inform challenges encountered and lessons learned.

